## Abstract

**Background:**

Since 2006, Burkina Faso has subsidized the cost of caesarean sections to increase their accessibility. Caesareans are performed by obstetricians, general practitioners, and nurses trained in emergency surgery. While the national caesarean rate is still too low (only 2 % in 2010), 12 to 24 % of caesareans performed in hospital are, in fact, not medically indicated. The objective of this study is to evaluate the effectiveness and analyze the implementation of a multi-faceted intervention to lower the rate of non-medically indicated caesareans in Burkina Faso.

**Methods:**

This study combines a multicentre cluster randomized controlled trial with an implementation analysis in a mixed-methods approach. The evidence-based intervention will consist of three strategies to improve the competencies of maternity teams: 1) clinical audits based on objective criteria; 2) training of personnel; and 3) decision-support reminders of indications for caesareans via text messages. The unit of randomization and of intervention is the public hospital equipped with a functional operating room. Using stratified randomization on hospital type and staff qualifications, 11 hospitals have been assigned to the intervention group and 11 to the control group. The intervention will cover 1 year. Every patient who delivered by caesarean during a 6-month period in the year preceding the intervention and the 6 months following its end will be included in the trial. The change in the rate of non-medically indicated caesareans is the main criterion by which the intervention’s impact will be assessed. To analyze the intervention process, a longitudinal qualitative study consisting of deliberative workshops and individual in-depth interviews will be conducted. The target outcome is a 50 % reduction in the rate of non-medically indicated caesareans.

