### Inclusion and exclusion criteria

A hospital was eligible for the trial if it had a functional operating room and had performed at least 200 caesareans in 2012. Twenty-two public hospitals were included in the trial between May and June 2014, out of a total of 24 eligible hospitals (91.6 %). Two university hospitals were excluded due to the high number of personnel in training. The 22 hospitals in the trial are representative of Burkina Faso’s current health system, spanning the full range in terms of context (urban versus rural), level of care (district and regional hospitals) and qualifications of health personnel. This process thus guaranteed a certain external validity of the results.

The intervention directly targets health professionals who provide obstetric care in the participating hospitals, while indirectly targeting the women giving birth there. The health professionals have been trained in the management of labour and delivery, with some also trained to perform caesareans. All health professionals involved in managing deliveries in their institutions were included in the study (*n* = 978). This total consisted of obstetricians and gynaecologists (*n* = 39), general practitioners (*n* = 32), physician anaesthetists (*n* = 3), nurses (*n* = 463), and midwives (*n* = 441). Maternity services personnel who were not involved in obstetric care in the labour room were excluded from the trial (*n* = 446).

The first 100 women with caesarean deliveries in the 22 hospitals during a 6-month period in the year preceding the intervention (May 2 to November 2, 2014) were included in the study. The first 100 women with caesarean deliveries in the 6 months following the end of the intervention will also be included. As the intervention will last 1 year, the pre- and post-intervention data collection periods will cover the same months of the year to avoid any seasonality bias. Women whose caesareans were performed in another hospital and who were subsequently transferred to a participating hospital will be excluded from the study.

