### Randomization and allocation

In February 2015, after a 6-month pre-intervention study, hospitals were allocated randomly to either the intervention or control group. Participating hospitals were grouped into three strata corresponding to different types of hospitals: regional hospitals, district hospitals in the two largest cities (Ouagadougou and Bobo Dioulasso), and district hospitals outside those two cities. All participating hospitals were randomly allocated simultaneously to minimize the risk of allocation bias [76, 77]. To prevent imbalance regarding the level of care in each stratum, block randomization was used to generate the allocation sequence [76, 77]. Investigators were informed of the allocation just before the intervention was implemented in the intervention group.

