### Analysis strategy

For evaluating the effectiveness of clinical audits in reducing NMIC rates, the unit of analysis is the patient. The main tests will be intention-to-treat analyses. A first descriptive analysis will be done to verify group comparability in terms of the characteristics of hospitals and patients included in the pre-intervention period. The primary analyses will take into account inter- and intra-cluster variability. We will use generalized estimating equations (GEE) to adjust the variance estimation for the intervention’s effect on inter-dependence of the measured events (NMIC or not) among patients of the same hospital [79]. The exchangeable structure of the residual covariance matrix will be used to represent the intra-cluster correlations. The same approach will be used to test the effectiveness of CBCAs in relation to resource improvement (complexity score), medical practices (caesarean quality score), and reductions in maternal and perinatal mortality. The intervention’s effect on the NMIC rate will be estimated from the odds ratio (95 % CI) based on the GEE approach and tested with the two-sided Wald test (α = 0.05) [79]. The intervention’s effects will be evaluated systematically both without adjustment and with adjustments on the stratification variables (type of hospital) and on the other baseline characteristics selected a priori, whose distribution could, even with randomization, be unbalanced between the two groups.

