Preliminary analyses will test whether the intervention’s effects vary according to hospital type, using chi-squared likelihood ratio tests with 2 degrees of freedom for hospital–intervention interaction. If the test does not reject the null hypothesis with α = 0.05, the interactions will be eliminated from the final model, which will enable the overall effect of the intervention to be estimated. However, if the interactions are statistically significant, subgroup analyses will be done to estimate the effects of the intervention separately for each type of hospital (district vs. regional), with a power of less than 90 %. A similar approach will be used to test whether the intervention’s effects depend on: 1) the caesarean rate in the pre-intervention period; 2) the initial knowledge score in the pre-intervention period; or 3) patient characteristics (age, parity, previous caesarean, prenatal care, referral for delivery) and any other variables distributed unevenly among groups in the pre-intervention period. In all secondary analyses, the intervention’s effects will be estimated from the adjusted odds ratio using the GEE approach, which generalizes the logistic regression to clustered data [79]. To analyze the implementation and heterogeneity of effects, interviews will be fully transcribed into a word processor program. Subsequently, qualitative data will be coded and organized using QDA Miner software and then subjected to content analysis [80].

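### The abstract and the randomization section disagree on the stratification factors, and a three-type interaction test is followed up with only two subgroups

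*Protocol article*

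**What the plan says.** **How hospitals were stratified.** The abstract (Methods) describes the allocation of 11 hospitals to each group in these words: "Using stratified randomization on hospital type and staff qualifications". The section Randomization and allocation reads: "Participating hospitals were grouped into three strata corresponding to different types of hospitals". It lists regional hospitals, district hospitals in Ouagadougou and Bobo Dioulasso, and "district hospitals outside those two cities". It does not mention staff qualifications. On blocking it says: "To prevent imbalance regarding the level of care in each stratum, block randomization was used to generate the allocation sequence".

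**How the analysis uses the strata.** Analysis strategy plans the intervention effect both without adjustment and with "adjustments on the stratification variables (type of hospital") and other baseline characteristics chosen a priori. It does not say which of the two estimates carries the two-sided Wald test at 0.05.

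**How heterogeneity is handled.** The same section tests the interaction of hospital type and intervention on 2 degrees of freedom at 0.05. If the test is significant, effects are to be estimated "separately for each type of hospital (district vs. regional").

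**The concern.** Three things are unsettled.

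1. Both descriptions of the randomization concern an allocation already carried out, yet the short one names a factor that the dedicated section lacks. Condensation normally loses detail rather than adding it. A reader cannot tell which factors the analysis has to reflect.
2. The follow-up to the interaction test uses fewer groups than the test. If the effect differs between big-city and other district hospitals, the test can reject, but the prescribed estimates average over exactly that difference.
3. With two versions of the main estimate and none named as primary, the version that ignores the strata could become the headline result. It gives up whatever precision the stratification was meant to bring.

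**Working it through.** **Degrees of freedom.** With two arms, interaction df = (number of hospital types − 1) × (2 − 1).
- Three types, as in Randomization and allocation: (3 − 1) × 1 = 2. This reproduces the article's figure.
- District versus regional: (2 − 1) × 1 = 1. This does not.

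The test therefore belongs to the three strata and the follow-up does not.

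**The statements side by side.**

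| Place | Factor | Levels |
|---|---|---|
| Abstract, Methods | hospital type and staff qualifications | not given |
| Randomization and allocation | hospital type | 3 |
| Analysis strategy, adjustment | type of hospital | not given; consistent with 3 |
| Analysis strategy, interaction test | hospital type | 3 (2 df) |
| Analysis strategy, follow-up | hospital type | 2 |

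Staff qualifications appears as a stratifier only in the abstract. It is not simply another name for hospital type, because Inclusion and exclusion criteria lists the two as separate attributes: "level of care (district and regional hospitals) and qualifications of health personnel". If level of care means district or regional, as there, it is constant within each of the three strata, so blocking within strata cannot be what balances it. That sentence does not help to settle what was done.

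**What the two-group follow-up can miss (illustration; all odds ratios assumed).** Take 0.5 in big-city district hospitals and 1.0 in other district hospitals, with equal weight. The pooled district odds ratio is about exp[(ln 0.5 + ln 1.0)/2] = 0.71, which describes neither stratum. If the regional odds ratio were also 0.71, the follow-up would show two equal effects after a significant test for heterogeneity.

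**Cost of ignoring the strata in the unadjusted estimate.** Inputs: ICC 0.02 (Sample size calculation); 76 cases per hospital, which is 76 % of 100, since the four indications made up 76 % of caesareans before the intervention (Assessment criteria). The share of between-hospital variance explained by the strata is not in the document and is assumed.

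The variance of a hospital proportion is proportional to ICC + (1 − ICC)/76 = 0.0200 + 0.0129 = 0.0329.

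| Assumed share explained | Remaining variance | Unadjusted SE / adjusted SE |
|---|---|---|
| 0 % | 0.0329 | 1.00 |
| 10 % | 0.0180 + 0.0129 = 0.0309 | √(0.0329/0.0309) = 1.03 |
| 30 % | 0.0140 + 0.0129 = 0.0269 | 1.11 |
| 50 % | 0.0100 + 0.0129 = 0.0229 | 1.20 |

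**Price of adjusting.** Two more parameters move a t critical value from 2.086 (20 df) to 2.101 (18 df), a change of 0.7 %. If staff qualifications was also a stratifier, at an assumed 2 or 3 levels, there would be 6 or 9 cells, with 22/6 = 3.7 or 22/9 = 2.4 hospitals per cell.

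**The case against.** The strongest reply is that the detailed text is coherent. The randomization section, the adjustment and the 2-df test all agree on three hospital types, and the only dissent is one clause in an abstract. This stands. A reader might infer that stratification is stated three ways, or that the model does not match the groups randomized. The document supports neither reading. District versus regional is a subgroup split and makes no claim about how hospitals were allocated. The adjusted model lacks a stratifier only if the abstract is right, and even then staff qualifications could enter among the a priori covariates, though it is not named there.

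It can also be said that a strata-adjusted estimate is already planned, and that a condensed article may leave the choice of primary estimate to the analysis plan. The first part stands: the standard error figures apply to the unadjusted estimate only. They do not measure the harm from the conflicting descriptions or from the subgroup mismatch. The second part lowers the weight of that element. It does not remove it, because the article places two versions side by side without ranking them.

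Finally, the follow-up is a conditional secondary analysis that the article admits has less than 90 % power, and its parenthesis may be loose shorthand. That limits the damage. The words as written still fix two groups after a three-group test.

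**Conclusion.** Two inconsistencies are established from the text alone: the abstract and the randomization section conflict on staff qualifications, and the two-group follow-up does not match its own 2-df test. The document does not settle which account of the stratification is right.

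The missing designation of a primary estimate is a lesser, related weakness. Leaving the strata out errs on the conservative side. The loss runs from nothing, through about 3 % on the standard error at an assumed 10 % of variance explained, to 11 to 20 % at an assumed 30 to 50 %. Nothing in the document says where in that range this trial lies, so the upper figures should not be read as the cost of the plan. The sample size figures are unaffected. The point is worth correcting and does not threaten the validity of the trial.

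**What to change.** 1. Check the allocation list and state the stratification factors once, in the same words in the abstract, Randomization and allocation, and Analysis strategy. Clarify in the same edit what the blocking was meant to balance.
2. Name as primary the GEE model adjusted for the strata actually used: three-level hospital type, plus staff qualifications only if it was on the list. Keep the unadjusted estimate as supportive.
3. After a significant 2-df test, report effects for the same three hospital types. If district versus regional is the comparison wanted, test it on 1 df instead.

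The first item is wording only. The second uses about two model degrees of freedom out of 22 hospitals, and more if staff qualifications was a stratifier, when cells become small. The third gives less precise estimates in three subgroups than in two.

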### Assessment criteria

These criteria were measured for a 6-month period (May 2–November 2, 2014) preceding the intervention year and will be measured again in the 6 months following the end of the intervention, corresponding to the same months of the year.

The primary assessment criterion is the NMIC rate.

We conducted a literature review to discern the diagnostic reasoning underlying evidence-based indications for caesareans. The four main indications for caesareans in Burkina Faso are: previous caesarean, prolonged/obstructed labour, pre-eclampsia, and acute foetal distress. In the 22 participating hospitals in the pre-intervention study, these four indications accounted for 76 % of all caesareans performed. The relevant references [47–70] were consulted and used to generate a provisional list of good practice criteria. Preference was given to evidence obtained through randomized controlled trials, considered the most rigorous. The provisional list of criteria was sent to 16 international and national experts (gynecologist-obstetricians, midwives, and a public health physician, see Additional file 10). The experts gave their opinions on the relevance of each criterion and proposed others. The criteria retained were those validated by at least two-thirds of the experts. We then developed clinical decision trees (algorithms) for managing the four main indications for caesareans and derived the criteria for NMIC.

The NMIC criteria are presented in Table 1. For each indication, all the criteria are considered simultaneously. A caesarean is judged to be non-medically indicated when all the criteria are met or when they are not documented and no opposing medical indication is provided. The NMIC rate was calculated for each hospital. This rate is the proportion of NMICs among all the caesareans performed for the four indications during the same period.

**Table 1 Tab1:** Criteria for non-medically indicated caesareans ^a^

Previous caesarean section	Prolonged/obstructed labour

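### The article does not fix one primary analysis: the main criterion is worded as a change and as a rate, unadjusted and adjusted odds ratios are unranked, the stratifiers differ, and the hospital's baseline NMIC rate is not a named covariate

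*Protocol article*

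**What the plan says.** **Main criterion.** The Abstract (Methods) states "The change in the rate of non-medically indicated caesareans is the main criterion" for judging impact. The body, under Assessment criteria, states "The primary assessment criterion is the NMIC rate", with measurement in a six-month period before the intervention year and again in the six months after it. The same section records that "The NMIC rate was calculated for each hospital".

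**Model.** Under Analysis strategy, the effect on the NMIC rate "will be estimated from the odds ratio (95 % CI) based on the GEE approach", with an exchangeable working correlation and a two-sided Wald test. Effects are to be evaluated "both without adjustment and with adjustments on the stratification variables (type of hospital) and on the other baseline characteristics selected a priori". Those other characteristics are not listed, and neither version is called primary. No period term, arm-by-period term or baseline NMIC rate is named.

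**Strata.** The Abstract says "Using stratified randomization on hospital type and staff qualifications". Randomization and allocation says the hospitals were "grouped into three strata corresponding to different types of hospitals": regional, district in the two largest cities, and district elsewhere. Analysis strategy also gives only hospital type as the stratification variable.

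**Sizing.** Sample size calculation asks for 2,200 records from 22 hospitals, with two-sided α of 5%, 90% power, a 50% reduction, 100 caesareans per hospital, ICC 0.02 and a variance inflation factor of 3.

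**The concern.** A change from baseline, a post-period comparison and a baseline-adjusted post-period comparison are different analyses with different variances. The first needs an arm-by-period contrast, which the described model does not contain. An unadjusted and a covariate-adjusted odds ratio are also different quantities, so leaving them unranked is more than a matter of precision. With only 22 hospitals, these results could fall on different sides of significance, and the text would let any of them be presented as the primary result.

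The hospital's own pre-intervention NMIC rate is an obvious prognostic covariate and is already in hand. A plan that does not name it probably gives up precision. The disagreement over stratifiers leaves open which design variables belong in the model.

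**Working it through.** **1. Reproduce the plan's figure.** VIF = 1 + (100 − 1) × 0.02 = 2.98, stated as 3. The control rate is not given in the sample size section; Background gives 12% to 24%. Assume 15% falling to 7.5%:

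n per arm = [1.96 × √(2 × 0.1125 × 0.8875) + 1.2816 × √(0.15 × 0.85 + 0.075 × 0.925)]² / 0.075² = 371 before inflation.

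371 × 3 × 2 = 2,226, close to 2,200. At control rates of 12%, 18% and 24% the same formula gives 2,862, 1,806 and 1,284. So 2,200 is recovered only with an assumed rate near 15%. It also equals 22 × 100, which is one period; both periods together would be 4,400. The sizing thus fits a post-period comparison of two proportions.

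**2. Variance of the candidate analyses.** Let CAC be the cluster autocorrelation (assumed; not in the document). The pre/post correlation of hospital rates is r = [m × ICC / (1 + (m − 1) × ICC)] × CAC. For m = 100 this is (2 / 2.98) × CAC = 0.671 × CAC. Relative to post-only, the variance is 1 − r² with baseline adjustment and 2(1 − r) for a raw change.

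**3. Power** (15% vs 7.5%, 1,100 per arm, effective n per arm 1,100 / 2.98 = 369, normal approximation; post-only 89.9% throughout):

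| CAC | r | Adjusted: variance ratio | Adjusted: power | Change: variance ratio | Change: power |
|---|---|---|---|---|---|
| 0 | 0 | 1.00 | 89.9% | 2.00 | 62.6% |
| 0.5 | 0.34 | 0.89 | 93.0% | 1.33 | 80.0% |
| 0.8 | 0.54 | 0.71 | 97.0% | 0.93 | 91.9% |
| 1 | 0.67 | 0.55 | 99.2% | 0.66 | 97.9% |

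A raw change beats post-only only if r exceeds 0.5, that is, CAC above 0.5 / 0.671 = 0.745.

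**4. Sensitivity to records per hospital.** The NMIC denominator is the four main indications, which made up 76% of caesareans before the intervention. If 100 caesareans yield 76 eligible records, VIF = 1 + 75 × 0.02 = 2.5, effective n = 836 / 2.5 = 334 per arm and post-only power is 86.8%. Now r = 0.608 × CAC. At CAC 0.8 the change analysis has variance ratio 2(1 − 0.486) = 1.03, slightly worse than post-only, whereas with 100 records it was slightly better.

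**5. Sensitivity to degrees of freedom.** With 76 records and t-tests on 20 df (unadjusted) or 17 df (adjusted for baseline rate and three-level type), power is 83.6% unadjusted. Adjusted power is 83.5% at CAC 0.2 and 86.4% at CAC 0.5. At low autocorrelation the gain disappears.

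**The case against.** The strongest case against is that this is a condensed article. Exact model terms and covariate lists commonly sit in a statistical analysis plan, and the unlisted a priori baseline characteristics could include the hospital's NMIC rate. An abstract may also word an outcome loosely, and both body sections agree on hospital type as the stratifier.

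Part of this stands. A reader might infer that the baseline rate is excluded, or that pre-intervention data serve only to check comparability. The text does not support that: Analysis strategy plans adjustment for hospital type and baseline characteristics, and pre-intervention variables also enter the planned effect-modifier tests. Nor can one say that chance imbalance is left uncorrected, since an adjusted analysis is planned systematically. With randomised hospitals, omitting the baseline rate would cost efficiency, not validity. That the sizing is post-only is an inference from the record count, not a statement in the article.

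What does not fall away is what the article itself contains: two wordings of the main criterion, two unranked odds ratios for it, and two accounts of the stratifiers. Even if the baseline NMIC rate were on the unseen covariate list, the primary estimate would still be unnamed here.

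**Conclusion.** The point holds as an ambiguity over which analysis is primary, together with a likely, unquantified loss of precision. Under the stated assumptions the choice matters: against about 90% for post-only, power is about 90% to 99% with baseline adjustment and about 63% to 98% for a raw change. With 76 records per hospital, post-only power is about 87%.

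It would be tempting to quote a single power loss. The documents do not allow it. The 15% control rate and the autocorrelation are assumptions, the ranking of change against post-only depends on the records per hospital, and normal-approximation power ignores the degrees of freedom spent. At zero pre/post correlation nothing is lost.

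**What to change.** Before post-intervention data are analysed, name one primary analysis: post-intervention NMIC by GEE, with arm, the strata actually used in the randomisation and the hospital's pre-intervention NMIC rate (log-odds scale) as covariates. The strata are three-level hospital type, plus staff qualification if the allocation record shows that it was used. Make the unadjusted and arm-by-period analyses supportive. Align the Abstract, Assessment criteria, Randomization and allocation, and Analysis strategy on the criterion and the stratifiers.

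The cost is wording only: baseline data exist and post-intervention collection is already planned. The model spends about three hospital-level degrees of freedom (two for hospital type, one for baseline rate) out of 20, and more if staff qualification is added. If the pre/post correlation proves low, that cost may not be recovered.
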